## Abstract

**Background:**

Despite a decade of substantial investments in programs to improve access to primary care for Aboriginal mothers and infants, more than 50 % of Western Australian Aboriginal babies are still not receiving primary and preventative care in the early months of life. Western Australian hospitals now input birth data into the Western Australian electronic clinical management system within 48 hours of birth. However, difficulties have arisen in ensuring that the appropriate primary care providers receive birth notification and clinical information by the time babies are discharged from the hospital. No consistent process exists to ensure that choices about primary care are discussed with Aboriginal families.

**Methods/Design:**

We will undertake a population-based, stepped wedge, cluster randomized controlled trial of an enhanced model of early infant primary care. The intervention is targeted support and care coordination for Aboriginal families with new babies starting as soon as possible during the antenatal period or after birth. Dedicated health professionals and research staff will consult with families about the families’ healthcare needs, provide information about healthcare in the first 3 months of life, offer assistance with birth and Medicare forms, consult with families about their choice for primary care provider, offer to notify the chosen primary care provider about the baby’s health needs, and offer assistance with healthcare coordination at the time of discharge from the hospital.

We will evaluate this model of care using a rigorous stepped wedge approach. Our primary outcome measure is a reduced hospitalization rate in infants younger than 3 months of age. Secondary outcome measures include completed Aboriginal and Torres Strait Islander child health screening assessments, immunization coverage, and satisfaction of the families about early infant primary care. We will also assess the cost effectiveness of the model of care.

**Discussion:**

This study will be conducted over a 4-year period in partnership with birthing hospitals and primary care providers including Western Australian Aboriginal Community Controlled Health Services and the new Primary Health Networks. The results of our trial will be used to develop improved primary care models and to improve health outcomes for all Aboriginal infants. These are vital steps toward more equitable health service delivery for the Aboriginal and Torres Strait Islander children in Australia.

**Trial Registration:**

Australian New Zealand Clinical Trials Registry

Registration number: ACTRN12615000976583

Date registered: 17 September 2015

## Background

The health of many Australian Aboriginal infants continues to be poor despite substantial investments from federal and state governments [1, 2]. The early infant period (from birth to 3 months of age, 0 to < 3 m) is the period when babies are most vulnerable, have the highest hospitalization rates, and are most in need of primary care services [3, 4]. Australian Aboriginal babies are scheduled for six contacts with primary care providers during this period for immunization (diphtheria, tetanus, pertussis (DTP), hepatitis B, Haemophilus influenzae type b, poliovirus, rotavirus, and pneumococcal vaccines) and for preventive care (screening for newborn blood spot, hearing, growth, development, oral health, ear disease, skin infections, family health and wellbeing, and the medical “6-week check”) [5, 6].

However, concern is increasing in the Aboriginal community that despite high-quality hospital-based maternity services, more than 50 % of Western Australian (WA) Aboriginal babies are not receiving the recommended scheduled primary care in the early infant period [2, 7]. More than 50 % of Aboriginal babies have not received Medicare registration in the first 7 days of life, and 40 % of the infants are overdue or have not received basic hepatitis B and DTP immunizations [8, 9]. Hospital admissions are twofold higher in Aboriginal than in non-Aboriginal babies during this period, and emergency department presentations are even higher [10–12].

Primary care services (that is, the first level of community healthcare) have the potential to have a major impact on the health of young Aboriginal infants during the early infant period [5, 7]. Community child-health nurses are considered the traditional providers of infant care during this period. However, general practitioners, practice nurses, and Aboriginal health workers at Aboriginal Community Controlled Health Services (ACCHSs), government health clinics, and general practice surgeries have been used by more than 90 % of Aboriginal families during the early infant period. These health professionals are not seen as traditional providers of early infant care, and many of these staff members lack the appropriate confidence and skills for managing young infants [13, 14]. Few of these nontraditional early infant care providers routinely receive birth notification information due to concerns from government departments about confidentiality and consent. Information is often provided using ad hoc systems including facsimile machines. In addition, few primary care providers receive the education, training, and tools needed to assist them in managing young infants. Primary care providers also often receive insufficient up-to-date information on the mother’s current concerns and needs and are unable to provide assistance with coordination of appointments and transport. This is especially the case for families who are most mobile; who move between regions, districts, and jurisdictions; and families who have not been able to connect with primary care providers [15–17].

New models of early infant primary care provision (for example, home visiting models, family-centered primary health care, and educational interventions) have been extensively evaluated and are highly efficacious in improving child health and developmental outcomes in Australia and internationally [18–22]. However, these programs involve the provision of new services and have problems with scale-up, cost effectiveness, and sustainability. The programs have also not been able to overcome the difficulties of maintaining contact with the most disadvantaged families who move between jurisdictions, the sharing of personal information with other primary care providers, and the engagement and communication between primary care services, especially in areas where families use multiple primary care service providers. New personally controlled electronic health records may assist with these issues but are new in implementation, and concerns exist that they will not benefit the most marginalized and disadvantaged families [17].

Personalized targeted support and care coordination from maternity hospitals has great potential to reduce barriers in provision of early infant primary care [23–26]. However, the application of current models has been limited in Australia and internationally due to restrictions within regions and jurisdictions. Models have also not been tested in complex environments with multiple nongovernmental organizations and primary care providers. Existing systems also continue to struggle with the provision of care to the most mobile families and have not tried to improve choice in primary care providers to families or assess the effect on access and utilization of services and health outcomes during the early infant period [25, 26].

The WA Department of Health (DOH) electronic clinical management system was developed in 2005 [27]. In 2013, all WA hospitals began inputting birth data into this clinical management system within 48 hours of birth and data are now being provided to government health services within 48 hours of birth. However, difficulties exist in ensuring that the appropriate primary care providers receive birth notification and clinical information by the time the babies are discharged from the hospital, and no process is currently in place to ensure that choices in primary care are discussed with Aboriginal families.

We have thus developed a population-based, stepped wedge, cluster randomized trial to test the effectiveness of an enhanced model of targeted support and early infant primary care coordination to improve access to primary care and the health of Aboriginal infants under 3 months of age in WA.

The primary outcome measure is a reduced hospitalization rate in infants aged younger than 3 months. Secondary outcome measures include completion of child health screening assessments, immunization coverage, and satisfaction of the families about early infant primary care. We will also assess the cost effectiveness of the model of care.

## Methods

### Study setting

This trial will be conducted across all of WA, which has a population of 2.5 million people and covers a geographical area of 2.5 million km^2^ [28]. WA has the most remote regions in Australia, with 95 % classified as ARIA (Accessibility/Remoteness Index of Australia) level 4 (remote) and 5 (very remote). Approximately 40 % of the Indigenous WA population resides within these remote and very remote regions of WA [28]. In 2010, there were 29,160 births in non-Aboriginal and 2,013 births in Aboriginal women [27]. Identification of Aboriginal and Torres Strait Islander ethnicity is improving in records of hospitalizations, with 96 % being correctly identified in 2011 to 2012 [29]. Thirty-seven birthing hospitals are located in WA: 28 public (one tertiary maternity hospital, and 27 secondary hospitals) and nine private birthing hospitals.

Approximately 2,900 primary healthcare services currently exist in WA, including 20 Aboriginal Community Controlled Health Services (ACCHS), which provide health services to regional, rural, and remote communities across WA, as well as the metropolitan areas. Nearly 400 government community health clinics and more than 2,000 registered general practice clinics exist. All births are attended by a registered midwife who must complete a birth registration form within 48 hours of birth. The state has been divided into 22 distinct areas separated by geographic, tribal, and health service provider boundaries, which provide the basis for our clusters.

This study is being coordinated from the Princess Margaret Hospital for Children (PMH) in Perth.

### Trial design

This will be a stepped wedge, cluster randomized controlled trial (RCT) (Fig. 1). This is one of the most appropriate study designs for evaluating health system interventions [30]. Advantages include enhanced motivation from patients and health professional staff to participate because all clusters receive the intervention, the design is more ethical with quality improvement initiatives that are likely to involve more good than harm within the study population, and the study can reduce the required number of clusters and therefore requires less financial input [30, 31]. The intervention effect is estimated by the between-cluster (those awaiting the intervention and those receiving the intervention) and within-cluster (before and after) comparisons. All public birthing hospitals in WA have been grouped into 22 distinct geographic clusters and will be randomized in a “stepped” (staggered) order to receive our model of targeted early infant primary care or to continue with standard care. The trial will consist of a baseline period of 6 months, followed by four steps of 6-month duration. Five or six new clusters will receive the intervention at each step, and all hospitals and primary care clinics will receive the intervention by the end of the second year of the trial. The CONSORT cluster RCT and pragmatic trial guidelines will be followed [32, 33]. The trial profile is outlined in Fig. 2. The trial has been registered in the Australian New Zealand Clinical Trials Registry (ANZCTR) (Registration number ACTRN12615000976583).

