### Inclusion and exclusion criteria

Thirty-seven birthing hospitals are located in WA; 28 public (one tertiary maternity hospital and 27 secondary hospitals) and nine private birthing hospitals. All public birthing hospitals in WA with five or more annual births of Aboriginal babies will be invited to participate in the intervention. All Aboriginal mothers who give birth to a live baby will be invited to participate in the study. Mothers will be asked for their written informed consent to be part of the study and to have evaluation data collected. We will not exclude any women who deliver a preterm baby, babies who develop complications, or any unwell babies, as these babies are most likely to benefit most from the improved skills of their primary care workers.

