### Randomization

A stepped wedge, cluster randomized controlled trial design was chosen in which hospitals are allocated into geographical clusters and then randomized into two groups (intervention or control) within each of the five steps (Fig. 1). Twenty-five birthing hospitals included in the sampling frame have been grouped into 22 geographical clusters defined by postcode. As such, these clusters are the unit of randomization in this trial. The cluster randomization was completed using a random number generator in Excel. A member of the research team grouped the 25 hospitals into 22 clusters and labelled these clusters 1 to 22. A separate Excel spreadsheet was created with a column containing the numbers 1 to 22. No information about the corresponding hospitals was present in this document. The de-identified Excel file was given to our statistician, who was blinded to the corresponding cluster information. The random number generator was used to generate a number from 0 to 1 next to each number in the column containing the de-identified cluster data (numbers 1 to 22). The two columns were then sorted by the column containing the random number, from the smallest to the largest. Five steps are included in this stepped wedge design, each representing 6 months. During the first step, or the first 6 months, all clusters are controls. Allocation into the intervention or control group for the additional four steps is as described below. Using the sorted list provided by the statistician, the first five clusters were allocated to the intervention group in step 1. Once allocated to the intervention group, a cluster continues in the intervention group for the remainder of the trial. The remaining 17 clusters are allocated to the control group for step 1. For step 2, the six clusters that immediately follow the first five clusters in the list were allocated to the intervention group. In total, 11 clusters were allocated to the intervention group by step 2. The remaining 11 clusters were allocated to the control group. The next five clusters in the random number generator sorted list were allocated to the intervention in step 3. The remaining six clusters were allocated to the control group. The final six clusters were allocated to the intervention group in step 4. The intervention commencement will be staggered at 6 monthly intervals, and all clusters will receive the intervention by step 4.

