### The intervention group

The targeted support and care coordination intervention is outlined in Table 1. Initially we will work with birthing hospitals to understand gaps in infant care coordination and target project tools to meet local needs. These consultations will inform the specifics of the care coordination activities, which will include the following:

**Table 1 Tab1:** Description of the intervention

The following three components of the intervention will be implemented by dedicated infant healthcare coordinators:
Hospitals - Work with birthing hospitals to understand gaps in infant care coordination and target project tools to meet local needs.
Families - Meet families as soon as acceptable to the families after birth. Use the locally targeted care coordination tools for the following:
- consult with families about their health care needs,
- provide information about primary care services available for the first 3 months of the baby’s life,
- offer assistance with birth and Medicare registration forms,
- consult with families about their choice for primary care provider,
- offer to notify the chosen primary care provider about the baby’s health needs, and
- offer assistance with health care coordination at the time of discharge from hospital.
Primary care providers - Work with the family’s chosen primary care provider to achieve the following:
- ensure they receive birth and hospital details,
- offer tools and guidance on early infant primary care, and
- offer additional assistance and contact points with experienced community child health nurses, primary care networks and pediatricians.

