### Data analysis

Data analysis will be conducted on the basis of intention to treat, regardless of movement between clusters. The intervention effect will be estimated by the between-cluster (those awaiting the intervention and those receiving the intervention) and within-cluster (before and after) comparisons. An analysis of the primary outcome (any hospitalization in the first 3 months of life) will be conducted at the individual infant level and will use binary logistic regression incorporating generalized estimating equations (GEE) to account for the loss of independence due to clustering. The primary independent variable will be whether or not the baby received the intervention. This will give rise to an odds ratio for the effect of the intervention on the probability of early hospitalization. The analysis will adjust for individual covariates, for example, maternal age, which may differ between groups receiving or not receiving the intervention at a given step. Similar techniques will be used for comparison of emergency department presentations and immunization coverage.

A societal viewpoint will be taken for the economic evaluation where all costs and consequences to the mothers and the wider community will be considered. All direct (fixed and variable) costs will be considered and will include the monetary costs of the intervention and resources. Consequences will be measured as hospitalizations averted. Incremental direct costs will be calculated by comparing the costs generated by the intervention with the costs generated by the control arm of standard care. Incremental consequences will be calculated by comparing the number of hospitalizations in the intervention clinics with the number of hospitalizations in the control clinics. Incremental cost-effectiveness ratios (cost per infant hospitalization case averted) will be calculated by dividing the incremental direct costs by the incremental hospitalization cases averted. Sensitivity analysis (a method to determine the robustness of an assessment by examining the extent to which results are affected by changes in methods, values of variables or assumptions) will also be performed. Satisfaction with care will also be assessed descriptively. The process outcomes and implementation of the intervention will also be assessed descriptively.

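### The stepped wedge makes no allowance for transition at the switch, although local set-up is part of the intervention; on the natural reading this dilutes the effect, by an amount the article does not let one fix

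*Protocol article*

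**What the plan says.** **Periods.** Trial design (Protocol article): "The trial will consist of a baseline period of 6 months, followed by four steps of 6-month duration". Under Randomization, clusters enter in groups of five, six, five and six at 6-month intervals, and "Once allocated to the intervention group, a cluster continues in the intervention group for the remainder of the trial". Sample size calculation splits all 4,750 expected births of the 30 months into 2,375 control and 2,375 intervention. No births are left over for a transition.

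**Outcome.** Data analysis defines the primary outcome as "any hospitalization in the first 3 months of life". The window is therefore half a step long.

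**Set-up.** The intervention group section opens: "Initially we will work with birthing hospitals to understand gaps in infant care coordination and target project tools to meet local needs". It adds that these consultations shape the details of care coordination, and Table 1 lists the hospital work as one of three components. Development of project tools covers generic tools only, piloted in one hospital before the trial. The control group section gives control clusters standard care and no extra support. No passage dates the local set-up relative to the switch.

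**Exposure.** Data analysis announces intention to treat, but makes the main explanatory variable the individual baby's receipt of the intervention.

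**Start of delivery.** The Abstract allows a start in the antenatal period or after birth. Table 1 and the text after it have families met after birth.

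**The concern.** Two groups of births lie close to each switch, and the stated structure treats neither as special.

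1. *Births just after the switch.* If coordinators must first consult the hospital and adapt tools, the first births of the intervention period occur before any family is seen. Coded by allocation, they count as intervention but have had none.
2. *Births in the 3 months before the switch.* They are controls, but part of their outcome window falls after the cluster has switched. Inclusion and exclusion criteria expects benefit through providers, for unwell and preterm infants in particular: "these babies are most likely to benefit most from the improved skills of their primary care workers". Better provider skills could also reach infants already born.

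Both mechanisms pull the estimate toward no effect, in a trial planned at 80 % power. The first is the larger risk. The antenatal and after-birth descriptions also bear on it, because they decide which early births could have been reached at all.

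**Working it through.** **Inputs from the article.** 22 clusters; "the first five clusters were allocated to the intervention group in step 1"; at step 2 "the six clusters that immediately follow the first five clusters in the list were allocated to the intervention group"; "The next five clusters in the random number generator sorted list were allocated to the intervention in step 3"; the last six at step 4. Five 6-month periods, 39 births per cluster per step, ICC 0.017, 31 % versus 24.5 %, alpha 0.05, 80 % power, design effect 0.57, 4,300 infants.

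**Assumptions.** Equal cluster sizes, births spread evenly over time, two-sided alpha, linear scale, calendar time adjusted for, exposure coded by allocation.

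**1. The plan's own figures.** Woertman design effect with k = 4 steps, one baseline and one measurement per step:

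[1 + 0.017(4×39 + 39 − 1)] / [1 + 0.017(0.5×4×39 + 39 − 1)] × 3(1 − 0.017) / [2(4 − 1/4)]
= 4.298 / 2.972 × 0.3932 = 0.569, which matches the stated 0.57.

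Two proportions, 31 % versus 24.5 %, 80 % power: 744 per arm, 1,488 in total. 1,488 × 0.57 × 5 periods = 4,241, or 4,418 starting from 1,550 with a continuity correction. Both are within 3 % of 4,300, so the stated calculation is reproduced.

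**2. Births near the switch.**
- Control cluster-periods: 5×1 + 6×2 + 5×3 + 6×4 = 56. Intervention: 110 − 56 = 54.
- Births in the last 3 months before a switch: 22 × 0.5 = 11 cluster-periods, so 11/56 = 19.6 % of control births. On average half of their window lies after the switch.
- Births in the first L months after a switch: 22L/(54×6) = 6.8 %, 13.6 % and 20.4 % of intervention births for L = 1, 2 and 3.

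**3. Effect of a set-up lag.** Simple averaging over births would leave about 93 %, 86 % and 80 % of the effect. That understates the loss, because a stepped wedge gives births near the switch more weight. I therefore used a Hussey-Hughes model with generalized least squares: 30 monthly periods, 39/6 = 6.5 births per cluster per month, and the 5/6/5/6 sequence. The standard error is 0.0231, and power = Φ(r × 0.065/0.0231 − 1.96), where r is the share of the true effect that remains.

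| Assumed lag | r | Power |
|---|---|---|
| 0 months | 100 % | 80 % |
| 1 month | 86 % | 67 % |
| 2 months | 71 % | 52 % |
| 3 months | 57 % | 36 % |

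**4. Effect of windows that cross the switch.** Let s be the share of the effect that acts through providers and reaches infants already born, in proportion to the part of their window after the switch. With no lag, s = 0 gives no loss (80 % power), and s = 0.5 gives r = 89 % and power 71 %. With s = 0.5, a lag of 1 or 2 months gives 56 % or 40 %. The article gives neither s nor the lag.

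**5. Cost of leaving births out.** Without the 3 months before each switch, the standard error rises from 0.0231 to between 0.0258 and 0.0264, and power is 69 to 71 %. If 2 months after the switch are also dropped, it is 0.0277 to 0.0297 and about 59 to 65 %. The ranges depend on whether calendar time is modelled by month or by 6-month step.

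**The case against.** A reader might infer three stronger things, and the article supports none of them.

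- *That a fifth of control infants receive part of the intervention.* The 19.6 % is the share whose window crosses a date. Delivery is tied to the family around birth and discharge, and Table 1's provider work starts from the provider that a family has chosen. A baby born and discharged before the switch has no coordinator contact. What remains is indirect spill-over through provider skills. The Discussion accepts that provider training may contaminate other clusters, but nothing sizes it, and it may be nil. The remark about skills was made to explain why unwell babies are not excluded.
- *That set-up is scheduled after the switch.* No date is given, and a condensed article may leave scheduling to the full protocol. This stands as a limit on certainty. The natural reading still points that way: set-up is named as part of the intervention, control clusters get no extra support, and the birth counts leave no gap.
- *That early births are certainly labelled exposed.* This follows from intention to treat. If exposure is coded by receipt, an early birth not yet reached counts as unexposed and this dilution does not arise. That is no rescue, because coding by receipt gives up the randomized comparison.

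It is also fair that the lag and the provider share are assumptions. With both at zero, nothing is lost. Sensitivity analyses are commonly left to the analysis plan, so the absence of one is not the point here. The point is the stated period structure and the conflicting definition of exposure.

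**Conclusion.** The point holds in a limited form. The stated structure has no room for transition, local set-up is part of the allocated intervention, and the definition of exposure conflicts with intention to treat. Under coding by allocation, a lag of 1 to 3 months before families are seen would reduce power from 80 % to between 67 % and 36 %. The crossing windows add a smaller and more speculative loss: from none to about 9 percentage points of power, for a provider share between zero and one half. These sizes rest on the assumptions listed with the calculation and on lags that the article does not state. They show how sensitive the design is to births near the switch; they do not forecast what will happen. The change is worth making because it is cheap and, according to Trial status, recruitment had not begun.

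**What to change.** 1. Schedule local consultation and tool targeting to finish before each cluster's switch date, so that this date is the first day families are seen. State this in the protocol.
2. In the primary model, define exposure by cluster and by date of birth relative to the scheduled switch date. This replaces the variable based on receipt, which conflicts with intention to treat. It also agrees with the sample size section, which already counts births by setting.
3. Keep every birth in the main analysis. Pre-specify one sensitivity analysis of the primary outcome that leaves out, for each cluster, births in the 3 months before the switch and births between the switch and the first family seen.
4. Reconcile the antenatal start in the Abstract with the after-birth start in Table 1 and the text that follows it.

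**Cost.** Earlier set-up visits need scheduling effort in each cluster; the extra analysis uses data already collected. The main analysis loses no births. The sensitivity analysis is clearly less precise: about 69 to 71 % power without the 3 months before the switch, and about 59 to 65 % if 2 months after it are also dropped. It should be read as a check on the main estimate and not as a second test.
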